We evaluated statistical power to detect main effects and interaction effects in Hypotheses 3 and 4. Our power analyses reveal that we have an excellent chance of detecting significant main effects and interactions in our data. Hypothesis 3 uses a repeated measures design with two conditions. Assuming an attrition rate of 20%, which we achieved in *Mujer Segura*, we will have 384 subjects per group for a total of 768 subjects at the end of five years. We used findings from the parent project intervention with FSWs described in Preliminary Studies to estimate overall reductions in high-risk sex and incident STIs. We observed a 36% reduction in unprotected sex in the intervention (i.e., 18% vs. 36%), and a 40% decrease in overall STI incidence in the intervention group relative to the control (i.e., 20% vs. 38%). To estimate power in our sample, assuming a 36% reduction in unprotected sex at six-month follow-up, we calculated the following: N=384 per group, alpha = .05, and a 36% reduction in mean number of unprotected sex acts. If subjects in our experimental condition reduced the number of unprotected sex acts while the control condition did not change (i.e., group x time interaction), we would detect significant differences greater than 78% of the time. Power is slightly higher for STIs (i.e., .81). The addition of a covariate for fidelity to test hypothesis 4 does not substantially impact power estimates. Therefore, though our study is not designed to replicate findings from the parent project, we have sufficient power to detect differences between groups.

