***Intervention Study Participants (FSWs)***

The second set of participants in this research will be the FSWs who are recruited at each CBO to participate in the baseline and follow-up assessments and either the *Mujer Segura* counseling intervention or the “usual care” comparison condition. The recruitment goal for the study will be 960 female sex workers (FSWs) from the twelve anticipated sites (12 CBOs times 80 FSWs per site = 960). As with the staff participants (see above), we are uncertain whether the all of the currently projected sites will be able to meet this quota. We also face the uncertainty (particularly in the early phases of the study) whether, once the study has been started at a particular site, the staff will be able to carry it to completion due to factors beyond our or Mexfam’s control. Accordingly, we request flexibility in the per-clinic and overall figures for recruiting FSWs, up to a maximum of 1,090 for the entire study (in increase of 130, which is 13.5% more, or the equivalent of less than two additional sites).

We anticipate that participants will range in age from 18 to 50 years (mean approx. 33); mean level of educational attainment will be 6 years; 80% will be married or living in a common-law relationship; and 94% will have children.

Inclusion Criteria: To be eligible for this intervention, participants must be:

1) Biologically female,

2) At least 18 years old,

3) Report having exchanged sex for money, goods or drugs within the previous 30 days,

4) Report having unprotected vaginal or anal sex with a male client at least once during the previous month.

Exclusion Criteria:

1) Consistent use of condoms for vaginal and anal sex with all male clients during the previous month,

2) Known to be HIV+ or test HIV+ for the first time on-site at MexFam clinic,

3) Being under 18 years of age,

4) Being male or transgendered,

5) Being incapable of giving informed consent,

Because this study is designed to transport an established, efficacious intervention into a community-based setting, we must adhere to core elements of the established intervention, which was designed for women who are biologically female. In the original intervention design, transgendered persons were excluded because this subpopulation of FSWs would require different recruitment strategies and a targeted intervention to reflect unique sexual risk behaviors and sexual milieu.

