16. RISK/BENEFIT RATIO

We judge the importance of the knowledge to be gained from this study to be quite high. First, we expect to significantly increase scientific knowledge of the barriers and facilitating factors associated with implementation of an efficacious behavioral intervention in a high-risk population. Second, implementation of *Mujer Segura* in 12 Mexican cities has the potential for significantly reducing the number of new HIV infections and STIs among FSWs and their clients. This is true both for the participants in the active control condition and for the recipients of the *Mujer Segura* intervention, since in the original *Mujer Segura* study, participants in the active control condition also experienced decreased in frequency of unprotected sex (see [name] et al., Appendix 1), but due to the absence of a third, “passive” or untreated control arm, it was not possible to determine whether the incidence of HIV or STIs in the active control group declined relative to an untreated group. In view of the minimal risks and the fact that even control group participants are likely to benefit, we hold that the potential benefits predominate.

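### The 78% power for unprotected sex acts assumes an unchanged control arm, which contradicts the protocol's own account of the parent trial; the figure is too high if the 36% is the intervention arm's own fall

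*Protocol*

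**What the plan says.** Hypothesis 3 (section 5) predicts a greater reduction in risky sex with clients at six months under the experimental counselling than under standard counselling. Section 8, Aims 3 & 4, lists the intervention-by-time interaction among the primary independent variables.

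The power paragraph in section 8 gives its inputs as "N=384 per group, alpha = .05, and a 36% reduction in mean number of unprotected sex acts". It then sets the scenario, "If subjects in our experimental condition reduced the number of unprotected sex acts while the control condition did not change", identifies this as the group-by-time interaction, and concludes that "we would detect significant differences greater than 78% of the time". The paragraph claims an excellent chance of detecting effects and ends by calling the power sufficient.

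The 36% comes from the parent project: "We observed a 36% reduction in unprotected sex in the intervention (i.e., 18% vs. 36" (the last figure is also a percentage). The STI effect in the same sentence is worded differently, as "a 40% decrease in overall STI incidence in the intervention group relative to the control (i.e., 20% vs. 38" (again a percentage).

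Section 16 reports that in the parent trial "participants in the active control condition also experienced decreased in frequency of unprotected sex". It supports the risk/benefit case with "the fact that even control group participants are likely to benefit".

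**The concern.** The protocol uses a flat control arm to claim power and an improving control arm to justify risk and benefit. Both statements draw on the same parent trial. The comparator is active counselling that includes risk assessment and risk-reduction strategies (section 8, Phase One), so some control improvement is what the protocol itself expects.

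The interaction is the experimental change minus the control change. The whole 36% can be the interaction only if controls stay flat, or if the 36% has already had the control change removed. If neither holds, the trial is powered for a larger effect than it expects to see. The stated figure is already a little under the usual .80, so there is no slack. A null result on behaviour could then be read as failed implementation when it reflects low power.

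**Working it through.** **Inputs.** From the protocol: 960 women recruited, 1:1 allocation, 20% attrition, alpha .05, a 36% reduction, and stated power above .78 (taken as .78). Not in the protocol: the mean and SD of unprotected acts, the size of the control fall, and the sidedness of the Aim 3 test. Two-sided is assumed because section 8 states it for Aim 2.

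**Sample size.** 960 × 0.80 / 2 = 384 per group. This reproduces.

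**Stated power.** The .78 cannot be checked without a mean and SD. Treating the percentages as proportions does not give it: 18% against 36% with 384 per group has power above .999, and 36% against 23.04% (= 36% × 0.64) has power .977.

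**Back-solving.** Power .78 at two-sided .05 implies a noncentrality of 1.960 + 0.772 = 2.732. The standardised difference is 2.732 × √(2/384) = 0.197. If that equals 36% of the baseline mean, the implied SD of change is 0.36 / 0.197 = 1.83 baseline means. This SD is held fixed below. Power is Φ(noncentrality − 1.960), and c is the assumed control fall.

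**Reading A: 36% is the intervention arm's own fall.** The net effect is 0.36 − c, so the noncentrality is 2.732 × (0.36 − c)/0.36.
- c = 5%: 2.732 × 0.31/0.36 = 2.353, power .65
- c = 10%: 2.732 × 0.26/0.36 = 1.973, power .51
- c = 15%: 2.732 × 0.21/0.36 = 1.594, power .36

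**Reading B: 36% is relative to the control level at six months.** The net effect is 0.36 × (1 − c), so the noncentrality is 2.732 × (1 − c).
- c = 5%: 2.595, power .74
- c = 10%: 2.459, power .69
- c = 15%: 2.322, power .64

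**Reading C: 36% is already net of control change.** The noncentrality stays at 2.732 and power at .78, whatever c is.

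**Sidedness.** Repeating Reading A one-sided, with the SD back-solved again, gives .67 at c = 5%, .54 at 10% and .41 at 15%. The pattern is the same.

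**The unexplained bracket.** Read as levels, 18% against 36% is a reduction of 1 − 18/36 = 50%, not 36%. Read as falls of 18% in controls and 36% in the intervention arm, the net effect is 18 points, the noncentrality is 2.732 × 0.18/0.36 = 1.366, and power is about .28. Neither reading confirms what the 36% measures.

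**The case against.** The strongest reply is that the 36% may already be a between-arm effect. The bracket 18% against 36% stands beside 20% against 38%, which is explicitly intervention against control, and it has the same form with the lower figure first. Section 7 also reports the parent results, including fewer unprotected acts, in a sentence that compares intervention with control. On that view the flat control arm is only a convenient way to express a net difference, and power is unchanged. This stands as a possibility. A reader might infer that power is below .78 on any reading, but the documents do not support that. Against the net reading, the 36% is described as a reduction in the intervention, while the STI figure beside it is described as relative to control. The parallel brackets are also a weak guide, since 1 − 20/38 = 47%, not the 40% stated.

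The magnitudes are also open to challenge, and this too stands. The control falls are assumed, and the SD is back-solved from a figure that cannot be reproduced. It is then held fixed, although the spread of a count may shrink with its mean. The results illustrate the direction and do not estimate the shortfall.

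A reader might add regression to the mean, because entry requires this criterion: "Report having unprotected vaginal or anal sex with a male client at least once during the previous month". That adds little. One act in a month is weak selection, no size is given, and a fall common to both randomised arms cancels in the contrast. It matters only if the 36% includes it, which returns to the question of what the 36% measures.

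Nor should a reader infer an arithmetic slip. The group size reproduces, and the .78 is neither confirmed nor refuted. The fault lies in an openly stated assumption that conflicts with another section.

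**Conclusion.** The contradiction between sections 8 and 16 is established by the text. The direction of its effect is conditional. If the 36% is the intervention arm's own fall, as the wording suggests, or is relative to the control level at six months, then any control fall makes the .78 too high. If the 36% is already net, the .78 stands and only the description of the scenario is wrong.

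Under the stated assumptions (fixed implied SD, two-sided .05, control falls of 5 to 15%), power runs from .65 down to .36 on the first reading and from .74 to .64 on the second. The actual overstatement, if any, cannot be determined from the protocol.

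A reader might extend the point to the STI power of .81. The documents do not support that, because the STI effect is stated relative to control. The point should be fixed, but it is not critical: it concerns a power statement, and no endpoint, analysis, allocation or participant protection depends on the correction.

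**What to change.** In section 8, Aims 3 & 4:

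1. Delete the assumption that the control condition does not change.
2. State the parent trial's change in unprotected acts in each arm, with its SD, and explain the bracket 18% against 36%.
3. Say whether the 36% is net of control change.
4. Recompute the power for the net difference in change, stating whether the test is one- or two-sided.
5. Replace the 78%, and the claims of an excellent chance and of sufficient power, as they apply to unprotected sex acts. Leave the STI power of .81 out of this correction.

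The cost is one recalculation from parent-trial data that the sponsor should hold, and a few reworded sentences. Enrolment does not change. The drawback is that the stated power may become less favourable.

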7. PROGRESS REPORT/PRELIMINARY STUDIES

***Mujer Segura Intervention Trial Results***

Results of the first phase of *Mujer Segura* (NIH R01 MH065849, Project #051182) were described in the following article (see Appendix 1):

[name], T.L., Mausbach, B.T., Lozada, R., [name], H., [name], S.J., Fraga, M., Orozovich, P., Abramovitz, D., de la Torre, A., Amaro, H., Martinez, G., Magis-Rodríguez, C., and [name], S.A. Efficacy of a brief behavioral intervention to promote condom use among female sex workers in two Mexican-u.s. border cities. *American Journal of Public Health.* 98 (11): 2051-7, 2008.

After participating in our 35-minute theory-based intervention, FSWs randomized into *Mujer Segura* had a 40% decline in cumulative STI incidence (p=0.03). Incidence density for the intervention vs. control was 13.8 vs. 24.92 per 100 person-years (py) for STIs combined (p=0.03), and 0 vs. 2.01 per 100 py for HIV (p<0.001), with concomitant increases in total numbers and percentages of protected sex acts and decreases in total numbers of unprotected sex acts with clients (p<0.05) at six-month follow-up. These results establish a baseline for efficacy against which successive implementations of *Mujer Segura* at other sites within Mexico can be measured.

Our human-subjects experience with *Mujer Segura* was excellent. A total of 1,853 participants were recruited, and none complained about any aspect of her treatment. Participant confidentiality was effectively maintained throughout the study. This was due to thorough training of staff at all implementation sites on the importance of informed consent and participant confidentiality. The same training measures will be implemented in the present study at all implementation sites.

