***The Intervention: Level of the FSW***

A secondary aim of this study is to determine how FSW behavioral outcomes change concordant with the fidelity of the implementation of *Mujer Segura* at each CBO and with other organizational characteristics. FSW data will be gathered at baseline (prior to counseling) and again at six-month follow-up using measures employed in our previous work with Mexican FSWs (Project #051182), which was reviewed and approved by the IRB.

Baseline and Follow-up Interview. The baseline interview (~30 min) is theory-driven and has been administered to over 1,800 FSWs in Mexico-U.S. border cities. Per the recommendations of our Mexican collaborators, all measures will be administered by computer-assisted personal interviewing (CAPI). Reading ability is not a requirement of study participation. Using CAPI technology, the interviewer will read all questions and response categories to the participant and record the participant’s responses on a computerized form.In order to measure intervention effects, the interview will be repeated with each participant at a six-month follow-up appointment. The interview covers the following domains:

 Background Characteristics. These include socio-demographics, family background variables (e.g., number of children), and financial need (e.g., number of financial dependents).

 Contextual factors. Interview questions include working conditions: work setting (e.g., street), type of sex worker (e.g., brothel-based), nature of relationship with pimp or manager (if applicable) (e.g., control over client selection), client characteristics, demands for unprotected sex, amount received for protected vs. unprotected sex, and availability of condoms and sterile syringes.

 Substance Use. History, practices and environmental influences, including age at first use of alcohol and specific drugs, amount of alcohol consumed using the AUDIT; types of substances used alone and in combination, routes of administration, and injection practices.

 Mechanisms of Change. Consistent with our theoretical framework, we include measures of attitudes, intentions, and peer norms about safer injection and sex.

 HIV and STI Knowledge will be measured with an 18-item scale that assesses awareness of the importance of condom use with respect to HIV/STI prevention (alpha = 0.75 to 0.89).

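### The STI power of .81 does not follow from the rates quoted beside it (20% vs 38% gives above .999, and is a 47% decrease, not 40%); the parent-trial densities over six months give about .6 to .75 two-sided

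*Protocol*

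**What the plan says.** The power paragraph for Aims 3 and 4 (Protocol section 8, Data Analysis and Interpretation) says that its effect sizes come from the parent project as described in Preliminary Studies. For STIs it cites "a 40% decrease in overall STI incidence in the intervention group relative to the control (i.e., 20% vs. 38"%). The sample size is fixed by "Assuming an attrition rate of 20"%, which takes 480 per group to 384. The calculation for unprotected sex uses "N=384 per group, alpha = .05, and a 36% reduction in mean number of unprotected sex acts" and yields power just above 78%. The STI result follows directly: "Power is slightly higher for STIs (i.e., .81"). The paragraph gives no other STI rate, no follow-up period for the 20% and 38%, no test and no sidedness for this figure. It concludes that power to detect group differences is sufficient.

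The section named as the source (section 7, Mujer Segura Intervention Trial Results) says that women in the intervention arm "had a 40% decline in cumulative STI incidence (p=0.03"), and "Incidence density for the intervention vs. control was 13.8 vs. 24.92 per 100 person-years (py) for STIs combined". It contains neither 20% nor 38%.

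On follow-up in the present trial, section 8 says "FSW data will be gathered at baseline (prior to counseling) and again at six-month follow-up". The STI comparison is to be made by Poisson regression. Two-tailed testing at .05 is stated for Aim 2 only.

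**The concern.** A rise from 20% to 38% is a very large difference for 384 women per group, so a power as modest as .81 cannot come from it. The pair also does not match the percentage attached to it, nor any figure in the section cited as its source. A reader therefore cannot tell which control rate the trial was sized on.

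This matters because lower STI incidence is part of Hypothesis 3, and section 12 lists decreased HIV and STI incidence among the desired primary outcomes of the intervention study with the women. If the control rate is nearer to the parent-trial density than to 38%, the chance of missing a true effect as large as the parent trial's is well above the 19% that a power of .81 implies. The study asks whether efficacy is preserved in scale-up, so a null STI result needs to be read against a correct power figure.

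**Working it through.** **Inputs.** n = 384 per group, alpha = .05, rates of 20% and 38%, and a nominal 40% decrease (section 8, Aims 3 & 4). Densities of 13.8 and 24.92 per 100 person-years (section 7). Follow-up of 0.5 year (section 8, Level of the FSW). Two-sided testing is an assumption here; the one-sided case is in step 5.

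**Formula for two proportions.** Power = Φ[(d − z·s0)/s1], with d = p2 − p1, s0 = √(2·p̄(1−p̄)/n), s1 = √((p1(1−p1)+p2(1−p2))/n), z = 1.96.

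**Step 1: try to reproduce .81 from the quoted pair.**
- 20% vs 38%: d = .18, s0 = .0328, s1 = .0321. (.18 − 1.96 × .0328)/.0321 ≈ 3.61, so power = .9998.
- A 40% cut from 38% is .6 × 38% = 22.8%. 22.8% vs 38%: d = .152, s0 = .0332, s1 = .0327, argument ≈ 2.65, power = .996.
- One-sided testing only raises these. A continuity correction leaves the first at .9998.
- Power of .81 for 20% vs 38% needs only about 102 women per group.
- Full cluster inflation with the ICC of .03, which the protocol gives for staff measures and not for the women, still leaves .85 to .98 for 20% vs 38% (cluster sizes 80 to 32).

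The stated .81 is not reproduced.

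**Step 2: the percentage attached to the pair.** 1 − .20/.38 = .474, a 47% decrease, not 40%.

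**Step 3: the parent-trial densities over six months, as proportions.**
- Risk = 1 − exp(−rate × 0.5): 1 − exp(−.1246) = 11.72% and 1 − exp(−.069) = 6.67%. s0 = .0209, s1 = .0208, argument ≈ .46, power = .68.
- Risk = rate × 0.5: 12.46% vs 6.9%. s0 = .0213, s1 = .0212, argument ≈ .65, power = .74.
- A 40% cut from the control risk: 11.72% vs 7.03% gives .61; 12.46% vs 7.48% gives .64.

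**Step 4: the same densities by the planned type of test (Poisson, Wald on the log rate ratio).** Person-years per arm = 384 × 0.5 = 192.
- Expected events: 192 × .2492 = 47.8 and 192 × .138 = 26.5. Log ratio .591, SE = √(1/47.8 + 1/26.5) = .242, ratio 2.44. Power = Φ(2.44 − 1.96) = .68.
- 40% cut: 47.8 vs 28.7 events. Log ratio .511, SE .236, ratio 2.16, power = .58.

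**Step 5: one-sided at .05.** The six-month densities give .78 (exponential risks), .79 (Poisson Wald) and .83 (linear risks). With a 40% cut they give .70 to .75.

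| STI input, 384 per group | Two-sided | One-sided |
|---|---|---|
| 20% vs 38% | .9998 | above .9999 |
| Parent densities, six months | .68 to .74 | .78 to .83 |
| 40% cut from parent control density | .58 to .64 | .70 to .75 |
| Stated in the protocol | .81 | sidedness not given |

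Continuity correction lowers the two-sided proportion results to .63 to .70 (densities) and .56 to .59 (40% cut).

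**The case against.** **Sidedness.** The paragraph gives alpha without saying one- or two-sided, and a one-sided test on the six-month densities gives .78 to .83, which brackets .81. This stands to the extent that one cannot say .81 is unreachable from every STI rate in the protocol. It does not validate the figure: the paragraph names neither those densities nor a one-sided test, and with the 40% reduction it does name, one-sided power is at most .75.

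**Meaning of the pair.** The parallel clause on unprotected sex gives 18% vs 36% for a 36% reduction, which would fit if the two figures were within-arm reductions. If 20% vs 38% had that form, it would not be a pair of risks and step 1 would fall away. But the STI clause speaks of incidence in one arm relative to the other, and neither 20 nor 38 equals the stated 40. At best this shows that the input is unclear, which still has to be corrected.

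**Control rate.** Cities from the original project were excluded, so the parent density is not known to apply in the new ones. Section 9 also allows up to 1,090 women. After 20% attrition that is 1,090 × .8/2 = 436 per group, and .73 to .79 two-sided on the parent densities. Both points stand, and they are why the restated power should be a range. Neither reaches .81, and the stated figure is explicitly for 384.

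**Weight.** Section 8 calls the women's outcomes a secondary aim and says that replicating the parent trial is not the purpose. That lowers the stakes, but section 12 still lists STI incidence among the primary outcomes of this component.

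**Conclusion.** Wrong as written. The power of .81 does not follow from 20% vs 38% at 384 per group (above .999), nor from a 40% cut from 38% (.996), and the pair is a 47% decrease. This rests only on reading the pair as risks, as the sentence is worded.

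On the parent densities over six months, two-sided power is about .68 to .74, or about .58 to .64 for a 40% reduction. A true effect of parent-trial size would then be missed about 26% to 32% of the time, and a 40% effect about 36% to 42%. These figures assume a two-sided .05 test, 384 per group, no clustering and the parent control rate.

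Some further inferences are tempting but not supported:
- The 40% decline and the 45% implied by the densities (1 − 13.8/24.92) do not contradict each other. The first is cumulative incidence, the second incidence density.
- It cannot be said that 38% is incompatible with 24.92 per 100 person-years, because no period is attached to the 38%.
- It cannot be said that excluding women not at risk at baseline lowers power further. The protocol treats curable STIs found at baseline and excludes HIV-positive women, so the size of any loss cannot be derived.

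**What to change.** In the power paragraph for Aims 3 and 4:
- Base STI power on one consistent set of rates, and state their source, follow-up period, test and sidedness.
- Correct 20% vs 38%, or explain what it measures and over what period. Remove the mismatch with 40%.
- Restate the power. If the parent densities over six months are used with a two-sided test, that is about .6 to .75 at 384 per group. Give it as a range, with the control rate in the new cities named as an assumption.
- Qualify the conclusion of sufficient power so that it does not cover STI incidence beyond what the restated figure supports.

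The cost is text only. No procedure or sample size has to change, but a stated figure is likely to become less favourable.
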